## Methods

### Study

The study will take place at Beth Israel Deaconess Medical Center (BIDMC), a Harvard affiliated teaching hospital in Boston, Massachusetts. The care team will include a psychiatrist, social worker, and digital navigator. The psychiatrist and social worker will provide clinical treatment, education, and support for all participants. The digital navigator, as previously discussed, will be available for technology support and mindLAMP training to other care team members and research participants.

For this study, 50 participants will be enrolled and will not be financially compensated for their participation in TECC. Given the success of the pilot Digital Clinic program, including 50 participants is feasible and necessary to collect a diverse sample and see significant effects of different techniques on clinical assessments of depression and anxiety. This study will be open to any adult (18 years or older) who is interested in using smartphone technology to augment their mental health care. Participants are required to meet the criteria for either mild to moderate depression or anxiety as measured on the Patient Health Questionnaire-9 (PHQ-9) or Generalized Anxiety Disorder-7 (GAD-7) scale. Participants must have daily access to a smartphone, be willing to download the mindLAMP app, use their smartphone for mental health care (both in and outside of session time), and be open to learning about an array of clinical modalities (dialectical behavior therapy [DBT], cognitive behavioral therapy [CBT], short psychodynamic therapies). For participants who do not own a smartphone, the care team will help individuals sign up for a free phone through the US Federal Government’s Project Lifeline if they are eligible. Participants must also be affiliated with a BIDMC or Beth Israel Lahey Health provider and be available for eight clinical sessions (telehealth) over the course of 2-4 months. Until the Spanish language version of the mindLAMP app has been properly vetted, participants must be able to read, write, and communicate in English at an eighth grade level. Recruitment efforts for TECC include digital flyers and brief informational sessions for referring providers.

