**Figure 2 figure2:**
[figure not shown]
The Technology Enabled Clinical Care survey and data collection timeline. BASIS-24: Behavior and Symptom Identification Scale-24; GAD-7: Generalized Anxiety Disorder-7; PC-PTSD-5: Primary Care Posttraumatic Stress Disorder-5; PHQ-9: Patient Health Question-9; SUS: System Usability Scale; TAM: technology acceptance model; WAI-SF: Working Alliance Inventory–Short Form; WHO-5: World Health Organization Five.

Upon completion of each clinical session, participants will meet with the digital navigator to address any technology-related questions or issues. The digital navigator will also work with participants to create any additional mood-tracking surveys and retrieve smartphone senor data (if applicable). The mindLAMP app will be used in and outside of the session to allow participants to track their daily moods (PHQ-9 and GAD-7 scales) and practice clinical skills (through activities in the app).

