### Further Study Details

All participants will complete a written informed consent for this voluntary study. Participants will be able to withdraw from TECC anytime, just as they can withdraw from routine care at any time. Participants who miss four consecutive sessions will be asked to restart the protocol. During the study, if a participant’s clinical presentation significantly worsens, the clinical team will re-evaluate the participant’s involvement in the study. Intent-to-treat analysis will be applied so that data from all participants, even those who drop out, will be included in the outcomes.

The mindLAMP app meets federal privacy and security requirements, and has been institutional review board (IRB)–approved for use in clinical research. All data collected by mindLAMP will be securely transmitted directly to a server within the hospital network. Additionally, after receiving IRB approval, the TECC protocol will be registered with ClinicalTrials.gov.

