### Analysis

Analysis will include calculation of the effect size of TECC to reduce symptoms related to stress, anxiety, and depression. Analysis will also focus on assessing association between baseline factors, race, language, and education, as well as dynamic factors like working alliance and technology engagement patterns with changes in symptoms and use and adherence to the TECC protocol. We will assess relationships between these factors and clinical changes using generalized linear models and multiple regression analyses. Tests for dropout effects will be performed to see if outcome and covariate measures are associated with differences in engagement. If there are significant dropout effects, a logistic dropout probability model will be fit using the significant dropout outcomes and covariates measured at the start of the stage, and inverse probability weighting will be used with these model probabilities to account for dropout in each of the models. The age-matched control group will be used to compare changes related to clinical scores and calculate effect sizes using means and SDs.

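### Dropout is corrected only if a test in 50 participants reaches significance, so informative dropout can go uncorrected and the intent-to-treat promise has no stated means of delivery

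*Protocol article*

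**What the plan says.** The Study section sets the size: "For this study, 50 participants will be enrolled and will not be financially compensated for their participation in TECC". It gives no expected dropout rate. Further Study Details then makes an unconditional commitment: "Intent-to-treat analysis will be applied so that data from all participants, even those who drop out, will be included in the outcomes".

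The Analysis section describes a sequence.

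- **Test:** "Tests for dropout effects will be performed to see if outcome and covariate measures are associated with differences in engagement".
- **Trigger and variable selection:** "If there are significant dropout effects, a logistic dropout probability model will be fit using the significant dropout outcomes and covariates". The predictors are those measured at the start of the stage.
- **Correction:** "inverse probability weighting will be used with these model probabilities to account for dropout in each of the models".

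The models are described as follows: "We will assess relationships between these factors and clinical changes using generalized linear models and multiple regression analyses". The Analysis section does not say what is done about dropout if the tests are not significant. The significance level of the dropout tests is not stated either. PHQ-9 and GAD-7 are to be completed daily in the app (Interventions; Study Measures), so many people who leave will have supplied scores beforehand.

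**The concern.** The rule uses significance for two decisions: whether to correct at all, and which variables enter the weight model. In a sample this small, failing to detect a dropout effect says little about whether one exists, yet the plan then proceeds as if there were none. The second use has the opposite weakness. Among many candidate variables some will be significant by chance and enter the weights, while real predictors that miss the threshold are left out.

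The protocol itself gives reason to expect informative dropout. The Introduction hypothesises that app engagement and alliance go with clinical improvement. If so, those who disengage differ in outcome from those who stay. At stake are the pre-post effect sizes and the 50% response rate, both of which would look too good if people who do not improve are more likely to leave.

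**Working it through.** The plan states no power, dropout rate or effect size for this step, so there is no figure to reproduce. The sample size is justified only in words: "including 50 participants is feasible and necessary to collect a diverse sample and see significant effects of different techniques".

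**Inputs.** From the document: N = 50. Assumed: two-sided alpha 0.05; dropout of 10 to 40%; a difference d of 0.3, 0.5 or 0.8 SD between dropouts and those retained.

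**1. Power of the gate for one measure.** With n_d dropouts and n_c = 50 − n_d retained, the noncentrality is d / √(1/n_d + 1/n_c), referred to a noncentral t with 48 df (critical value 2.011). For 10 against 40, √(1/10 + 1/40) = 0.354. Then d = 0.5 gives 1.414 and power 28.3%; d = 0.8 gives 2.263 and power 60.2%. The difference detectable with 80% power is (1.960 + 0.842) × √(1/n_d + 1/n_c).

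| Dropout | d = 0.3 | d = 0.5 | d = 0.8 | Detectable at 80% power |
|---|---|---|---|---|
| 10% (5 v 45) | 9.6% | 18.0% | 38.3% | 1.32 SD |
| 20% (10 v 40) | 13.2% | 28.3% | 60.2% | 0.99 SD |
| 30% (15 v 35) | 15.9% | 35.5% | 71.9% | 0.86 SD |
| 40% (20 v 30) | 17.5% | 39.7% | 77.5% | 0.81 SD |

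**2. Several measures tested.** The plan tests outcomes and covariates in the plural, and any significant result opens the gate. By simulation at 10 against 40, with every measure shifted equally and correlations of 0.3 to 0.6 between measures (assumed):

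| Measures | Gate opens, d = 0.5 | Gate opens, d = 0.8 |
|---|---|---|
| 3 | 49–56% | 81–88% |
| 5 | 57–70% | 87–95% |

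If only one measure differs, the single-test figures are the relevant ones for that measure.

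**3. False triggers.** With k independent null tests the chance of at least one significant result is 1 − 0.95^k: 23% for k = 5 and 34% for k = 8.

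**4. Bias.** Simulation of 6,000 runs per scenario, with one dropout predictor correlated 0.5 with the outcome. Without weighting, the expected bias is correlation × d × dropout proportion. For example, 0.5 × 0.8 × 0.4 = 0.16 SD, which the simulation matches. Bias in SD units, positive meaning that the retained participants look better:

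| Dropout, d | Gate opens | Never weighted | Gated rule | Gate shut | Always weighted |
|---|---|---|---|---|---|
| 20%, 0.3 | 13% | 0.028 | 0.017 | 0.019 | −0.002 |
| 20%, 0.5 | 27% | 0.054 | 0.029 | 0.038 | 0.004 |
| 20%, 0.8 | 59% | 0.079 | 0.019 | 0.048 | 0.001 |
| 30%, 0.3 | 17% | 0.045 | 0.026 | 0.032 | 0.000 |
| 30%, 0.5 | 36% | 0.075 | 0.032 | 0.047 | 0.000 |
| 30%, 0.8 | 71% | 0.121 | 0.022 | 0.070 | 0.003 |
| 40%, 0.3 | 18% | 0.059 | 0.035 | 0.042 | −0.001 |
| 40%, 0.5 | 39% | 0.100 | 0.041 | 0.065 | 0.002 |
| 40%, 0.8 | 76% | 0.163 | 0.028 | 0.094 | 0.009 |

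**5. A second mechanism.** Here about 20% drop out, depending on mid-treatment change (log-odds 0.8 per SD), over 3,000 runs with a true mean change of −0.58 SD. The gate opened in 54% of runs. The gated rule gave −0.604, so the excess is 0.024/0.58, about 4%. In runs where the gate stayed shut the excess was about 9%. A regression adjustment that was always applied gave −0.577.

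**The case against.** The strongest defence is that the article condenses a fuller plan. It names a recognised dropout adjustment, and the average bias left by the gate is small. Four stronger readings are tempting, and the documents do not support them.

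- **That the fallback is a completer analysis.** The article never says so. Predictors taken at the start of the stage suggest stage-wise modelling, in which people may contribute until they leave, and nothing excludes the daily scores they supplied. What can be said is that no method is named for that branch.
- **That the Analysis section contradicts the intent-to-treat statement.** It excludes nobody. It leaves the promise without a stated means of delivery. Weighting alone does not supply one, because it reweights observed outcomes.
- **That the effect would be about 17% too large, with correction skipped 72% or 40% of the time.** The 17% describes analyses that are never weighted (−0.678 against −0.58 in the second mechanism), which is not the planned rule. The skip rates are 1 minus the single-test power at 20% dropout, whereas several measures are tested.
- **That the confidence intervals are invalid.** Ignoring a pre-test can distort intervals, but the Analysis section mentions none and coverage was not calculated.

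The defence does not rescue the gate. The rule is stated explicitly, so this is a choice of method and not an omitted detail, and the gate brings no compensating benefit.

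**Conclusion.** The concern holds in a limited form. A significance test in 50 participants is a poor basis for deciding whether to correct for dropout and with which variables. On a single measure it misses a 0.5 SD difference in about 60 to 82% of studies across 10 to 40% dropout, and less often if several measures differ together. In the scenarios run, the gated rule leaves a bias of about 0.02 to 0.04 SD on average, and 0.02 to 0.09 SD when the gate stays shut.

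These sizes rest on assumed dropout rates, differences and a predictor–outcome correlation of 0.5; a stronger link would raise them. The direction favours TECC only if non-improvers are the ones who leave. Always-on weighting brought the bias close to zero, provided the dropout predictor is measured and the dropout model is right. The bias is modest, but the change is cheap and worth making before outcome data are seen.

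**What to change.** Remove the significance condition. Name one primary missing-data method that is always applied, covers all enrolled participants and uses their PHQ-9 and GAD-7 scores up to dropout. Either a mixed model for the repeated scores or inverse probability weighting without a gate would do, and the choice between them is partly preference. Fix the covariate list in advance instead of selecting by significance, and run the other method as a sensitivity analysis. The dropout tests can stay as description.

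For the 50% response rate, add a conservative sensitivity analysis that counts participants without an endpoint as non-responders. This is a stronger assumption than the one behind the score analysis, so it should not be the only result. Add a sentence to the Analysis section saying how it fulfils the intent-to-treat statement in Further Study Details.

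The cost is revised wording, standard software, slightly more analysis work, and possibly slightly less favourable estimates.

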**Methods:**

The TECC study will assess the acceptability and efficacy of this care model in 50 participants as compared to an age- and gender-matched cohort of patients presenting with similar clinical severity of depression, anxiety, or psychotic symptoms. Participants will be recruited from clinics in the Metro Boston area. Aspects of TECC will be conducted in both Spanish and English to ensure wide access to care for multiple populations.

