Stage 1 “Creating the Clinical Foundation”: This stage will allow participants to learn and practice shared decision-making by cocreating treatment goals, identifying thought patterns, and identifying coping skills and defense mechanisms. The goal of this stage is for participants to develop a broad understanding of their thoughts and behaviors while beginning to identify strengths and need areas. Participants will also be introduced to clinical language and definitions for shared language to be established.Stage 2 “Building Clinical Skills”: Expanding from the skills learned in stage one, this stage will focus on teaching and practicing cognitive defusion and behavioral activation techniques. The goal for this stage is to expose participants to practical therapeutic skills that can be used across many situations and symptom management.Stage 3 “Solidifying Clinical Gains”: This stage introduces participants to mindfulness techniques, a diary card–like model, and patient activation and empowerment skills. The purpose of this stage is to ensure participants grasp all technical skills and clinical language reviewed throughout treatment to make informed autonomous decisions regarding treatment preferences.

This yearlong study will follow a prospective longitudinal cohort design where all participants will receive the same treatment and smartphone interventions. Based on our own Digital Clinic pilot data, we hypothesize participants will report a treatment response rate—defined as 50% symptom reduction—of improvements in anxiety and depression within the 8 weeks of treatment compared to their initial baseline. We also hypothesize that both rates of app engagement out of sessions, as well as therapeutic alliance measured during sessions, will be correlated with clinical improvements and suggest a mechanism of action for TECC. Furthermore the study will test the feasibility of providing technology-enabled mental health care within an outpatient clinical setting via virtual telehealth visits, explore the linguistic and cultural appropriateness of the smartphone app (mindLAMP) used in the study, and analyze the symptom changes of anxiety and depression for all study participants.

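### The comparator is matched on age, gender and severity in the abstract but called only age-matched in the analysis, where changes are compared by means and SDs with no baseline adjustment named

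*Protocol article*

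**What the plan says.** The protocol article describes the comparator in two places.

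- **Abstract, Methods.** The 50 participants are assessed "as compared to an age- and gender-matched cohort of patients presenting with similar clinical severity of depression, anxiety, or psychotic symptoms".
- **Results, Analysis.** "The age-matched control group will be used to compare changes related to clinical scores and calculate effect sizes using means and SDs".

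Three other statements set the context.

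- **Introduction.** The study is a "prospective longitudinal cohort design where all participants will receive the same treatment and smartphone interventions". The hypothesis stated there concerns change from each participant's own baseline, with response defined as a 50% symptom reduction.
- **Methods, Study.** "Participants are required to meet the criteria for either mild to moderate depression or anxiety", measured on the PHQ-9 or GAD-7. Entrants must also be interested in using a smartphone in their care.
- **Results, Analysis, on modelling.** "We will assess relationships between these factors and clinical changes using generalized linear models and multiple regression analyses". The factors meant are baseline characteristics, working alliance and technology engagement. Inverse probability weighting is also planned, but for dropout, and only if dropout effects prove significant.

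The size of the control cohort is not given.

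**The concern.** The outcome is change in a severity score, so starting severity is the matching factor that matters most. It is present in the abstract's description and absent from the section that governs the calculation. A reader who selects controls from the Analysis section could pick a different group from a reader who uses the abstract.

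The estimator adds to the problem. Subtracting baseline removes a fixed difference between groups but not regression to the mean: a group that starts higher tends to fall further whatever care it receives. The same section names regression and weighting methods but gives them to other questions, which leaves the TECC-versus-control contrast on means and SDs.

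At stake is the only controlled effect size in the plan, and with it the abstract's aim of judging efficacy against other patients.

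**Working it through.** **Step 1: the two descriptions side by side.**

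| Feature | Abstract, Methods | Results, Analysis |
|---|---|---|
| Age | matched | matched |
| Gender | matched | not mentioned |
| Severity | similar | not mentioned |
| Estimator | not stated | changes, with effect sizes from means and SDs |
| Adjustment for this contrast | not stated | none named |

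**Step 2: can the plan's own figure be reproduced?** No. The number 50 is given without alpha, power, effect size, SD or control-group size. As context only, assume 50 versus 50, two-sided alpha 0.05 and 80% power. By the normal approximation the detectable standardised difference is (1.960 + 0.842) × √(2/50) = 2.802 × 0.2 = 0.56.

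**Step 3: size of the error if starting severity differs.** All inputs here are assumptions: a baseline imbalance of b SD, a pre-post correlation of r, equal variances at both times, and no true treatment effect.

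- Spurious difference in mean change, in baseline SDs: (1 − r) × b
- SD of change, in baseline SDs: √(2(1 − r))
- Spurious effect size, in SDs of change: (1 − r) × b / √(2(1 − r))

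For b = 0.5:

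- r = 0.3: 0.35 / √1.4 = 0.35 / 1.183 = 0.30
- r = 0.5: 0.25 / √1.0 = 0.25
- r = 0.7: 0.15 / √0.6 = 0.15 / 0.775 = 0.19

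For b = 0 the result is 0 at every r.

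**Step 4: simulation check.** 4,000 runs per setting, 50 versus 50, no true effect.

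| r | b | Unadjusted effect size (absolute) | False positives, unadjusted | False positives, baseline-adjusted |
|---|---|---|---|---|
| 0.3 | 0.25 | 0.144 | 10.6% | 4.7% |
| 0.3 | 0.5 | 0.299 | 31.8% | 4.6% |
| 0.5 | 0.25 | 0.128 | 9.5% | 4.9% |
| 0.5 | 0.5 | 0.251 | 23.5% | 5.0% |
| 0.7 | 0.25 | 0.098 | 8.0% | 5.1% |
| 0.7 | 0.5 | 0.194 | 15.3% | 4.8% |

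The baseline-adjusted estimates lay within 0.005 of zero. The simulation assumes that patients with the same baseline score follow the same course in both groups, so this good performance is partly built in.

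**Step 5: direction.** The group that starts more severe appears to improve more. If TECC starts worse, the error favours TECC. If the controls start worse, it counts against TECC. The document does not say which is likelier.

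The effect of a gender imbalance was not quantified; nothing in the document gives a basis for it.

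**The case against.** The strongest reply is that the Analysis section uses shorthand. It refers back to a control group with the definite article, the abstract's cohort is the only one introduced anywhere, and a group matched on age, gender and severity is also age-matched. On that reading the two places agree and the error in Step 3 is about zero. This is plausible and it stands. A reader might infer that matching is on age alone, or that the effect size is certainly confounded; the document says neither. What remains is that the text does not settle the point, and that no adjustment is named under either reading.

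Two other stronger readings also fail.

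- **Single cohort.** The Introduction says that all participants receive TECC. That is compatible with an external matched cohort and is no contradiction.
- **Psychotic symptoms.** One might infer that naming them in the match brings in a different population. They are not an entry criterion, but the Study section does not exclude them either, so participants may have them. The fair remark is only that no measure of them is named for the match, so similar severity is not clearly defined on the trial's entry scales.

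It can also be said that covariates are often left to an analysis plan. That holds for detail, but here the article does state an estimator, and it assigns its regression models elsewhere.

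Finally, baseline adjustment is not always less biased than change scores between non-randomised groups (Lord's paradox): it assumes that patients with equal baselines would evolve alike. This stands as a caution. It loses force once severity is also matched, because the baseline gap on which the two methods disagree is then small.

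**Conclusion.** The point holds in a limited form. The comparator is described differently in two places, and the only between-group effect size is to be computed from changes, means and SDs without a baseline adjustment tied to it. That effect size is open to confounding by starting severity and gender, and to differential regression to the mean, in either direction.

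The illustrative size is 0.19 to 0.30 SD of change for a 0.5 SD imbalance and a correlation of 0.3 to 0.7. The false-positive rate is then about 15% to 32% instead of 5%. The imbalance, the correlation and the 50 controls are all assumed, and the error vanishes if severity is in fact matched.

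The Introduction's within-participant hypothesis does not depend on this comparison. Nor would repairing the comparison make it causal: interest in smartphone care distinguishes TECC entrants from controls, and neither matching on these factors nor adjustment removes that.

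**What to change.** 1. Use the abstract's matching set (age, gender, baseline severity) in both the abstract and the Analysis section. Define severity on the trial's own PHQ-9 and GAD-7 scales. If psychotic symptoms stay in the match, name the measure.
2. Replace the raw comparison of means and SDs with a regression of follow-up score on group, adjusted for baseline score, age and gender. Allow for the matching in the standard errors, and report a confidence interval.
3. Fix one follow-up window for both groups. The Introduction speaks of 8 weeks, while the Study section allows the eight sessions to run over 2 to 4 months.
4. Describe the result as an observational comparison and state that self-selection into smartphone-based care remains.

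The cost is a change of wording and one extra model. A few participants may lack a match. The change is best made before the controls are selected.

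### Dropout weighting is tied to the regression models, and no dropout method is attached to the effect size against the matched control group, although intent-to-treat is promised

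*Protocol article*

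**What the plan says.** Three parts of the protocol article bear on this.

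- **Further Study Details** sets the analysis principle: "Intent-to-treat analysis will be applied so that data from all participants, even those who drop out, will be included in the outcomes".
- **Analysis, association strand.** Baseline factors and dynamic factors such as alliance and engagement are related to symptom change: "We will assess relationships between these factors and clinical changes using generalized linear models and multiple regression analyses". Dropout is then tested for. The correction is conditional, "If there are significant dropout effects, a logistic dropout probability model will be fit", and its scope is given as "inverse probability weighting will be used with these model probabilities to account for dropout in each of the models".
- **Analysis, efficacy strand.** The section opens with "Analysis will include calculation of the effect size of TECC to reduce symptoms related to stress, anxiety, and depression" and names no method there. Its last sentence brings in the matched control group to "compare changes related to clinical scores and calculate effect sizes using means and SDs". That sentence mentions no weighting, imputation or other treatment of dropouts.

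The Abstract gives changes in mood, anxiety and stress as the primary outcomes. Study Measures has the PHQ-9 and GAD-7 completed daily in the app and the other clinical scales before each visit.

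**The concern.** The article is not silent on dropout. It specifies a test, a logistic model, weights, and where the weights go. The only outcome models named before that scope statement are the generalized linear and multiple regression models for associations. A mean and SD of change is not one of them. Read as written, the correction protects the secondary association analyses and leaves the comparison with the control group uncovered, even when the dropout test is significant.

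That comparison is the figure readers will use to judge whether TECC works. The plan's own reasoning makes a bias in TECC's favour plausible. The Introduction hypothesises that app engagement and alliance go with clinical improvement, and the Discussion repeats the link for engagement. If the less engaged leave early and also improve less, an average over those with an end score would flatter the programme.

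**Working it through.** **1. Reading the scope.** The weights apply to models, and the models named are the regressions. The effect size is described afterwards, in its own sentence, by a different calculation. The intent-to-treat statement is general and exempts nothing. Side by side, the general promise covers the effect size, but the only stated mechanism for keeping it does not.

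**2. Inputs.** From the article: 50 TECC participants (section Study). Not in the article: a dropout rate, an SD, an expected effect, or the number of controls. There is no stated figure to reproduce, and everything below is illustration under assumptions.

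**3. Single-group mean change.** Let d be the dropout share and r the dropouts' improvement as a fraction of that of those who stay. The mean over all participants is (1 − d) + d·r times the mean of those who stay, so

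overstatement = 1 / ((1 − d) + d·r) − 1.

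| d | r = 1 | r = 0.5 | r = 0 |
|---|---|---|---|
| 20% | 0% | 1/0.90 − 1 = 11% | 1/0.80 − 1 = 25% |
| 30% | 0% | 1/0.85 − 1 = 18% | 1/0.70 − 1 = 43% |
| 40% | 0% | 1/0.80 − 1 = 25% | 1/0.60 − 1 = 67% |

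These percentages apply to the TECC group's mean change. They do not carry over to the between-group effect size, which also depends on the control group's change and on the SD.

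**4. On the SD scale.** Let g be the difference in mean change between those who stay and those who drop out, in within-group SDs. The mean of those who stay exceeds the mean of all participants by d·g. If the control mean is unaffected, the between-group difference shifts by the same amount.

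- d = 20%, g = 0: 0.
- d = 20%, g = 0.5: 0.2 × 0.5 = 0.10 SD.
- d = 20%, g = 1.0: 0.2 × 1.0 = 0.20 SD.
- d = 40%, g = 1.0: 0.4 × 1.0 = 0.40 SD.

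For scale, the standard error of a mean change with n = 50 is √(1/50) = 0.14 SD. For a difference of 50 against 50 (an assumed control size) it is √(2/50) = 0.20 SD.

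**5. The trigger.** The weights are used only after a significant dropout test. With 40 staying and 10 leaving and a 0.5 SD difference between them on a tested measure, the standard error is √(1/40 + 1/10) = 0.354 SD. Power at two-sided 5% is then about Φ(0.5/0.354 − 1.96) = 29%. For a 1.0 SD difference it is 81%.

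**The case against.** The strongest reply is that the article nowhere says the means are unweighted or limited to completers. Means and SDs can be weighted, or built on imputed or last available scores, and the intent-to-treat statement is explicit and general. PHQ-9 and GAD-7 are requested daily from at least a week before the first session, so many early leavers will have a baseline score and some later score. How a dropout's change is formed may also be left to the full protocol or analysis plan, which is not shown.

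Much of this stands. A reader might infer that the efficacy figure is a completers' result, but the documents do not support that. No sentence restricts the calculation to completers, and one says dropouts are included. A reader might also infer that each dropout breaks a matched pair. The article describes a matched cohort, not one-to-one pairing or a paired analysis, so that cannot be claimed either. Nor does the article show that controls have repeated scores.

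The core is not answered. The article does specify a dropout method and its scope, and that scope omits the control comparison, so this is more than a detail left for later. Daily scores make a better estimate feasible but do not show that one is planned. A last score in week 2 is not an 8-week change, and the scales completed before visits will normally stop when the visits stop.

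**Conclusion.** The point holds as a mismatch between the intent-to-treat promise and the stated dropout method. The Analysis section attaches weighting to the regressions and none to the effect size against the control group, so nothing stated there delivers the promise for the efficacy comparison. Any bias arises only if two things are true: the effect size is computed from simple means of available end-of-treatment changes, and dropouts improve less than those who stay. Its size cannot be derived from the documents. Under the assumed values above it runs from nothing to an overstatement of 11% to 25% in the TECC mean change at 20% dropout, or 0.10 to 0.20 SD for gaps of 0.5 to 1.0 SD. This should be corrected, because it concerns the main efficacy figure and the remedy is cheap.

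**What to change.** In the Analysis section, state how dropouts enter the effect size. Either of two routes would do:

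- Extend the inverse probability weights to the means and SDs behind the effect size. This needs the fewest words. If the significance trigger is kept, the weights will often not be applied in a sample of this size, as step 5 shows.
- Estimate the TECC mean change from a repeated-measures mixed model using every available PHQ-9 and GAD-7 score of all 50 participants, dropouts included, and use that estimate in the control comparison. This needs no trigger.

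Report any completers-only effect size as supplementary. Clustering by matched pair belongs in the analysis only if one-to-one matching is actually used.

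The cost is a wording change and a little more programming. No new TECC data are needed, since the two scales are already collected daily. The effect size may come out less favourable.
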